## 4.4 Time & Events Table

**Table 1: Time & Events**

| Study Assessments                                                                                             | Pre-Study/
Screening  | Baseline (T1)  | MTM-Kids Meal Deliveries  |                 |                  |
|---------------------------------------------------------------------------------------------------------------|--------------------------------------|----------------------------|---------------------------------------|-----------------|------------------|
|                                                                                                               |                                      |                            | 4 weeks
(T2)                       | 8 weeks
(T3) | 12 weeks
(T4) |
| Eligibility Verification                                                                          | ×                                    |                            |                                       |                 |                  |
| Informed Adult Consent/Parent Permission/Adolescent Assent/HIPAA Authorization                    | ×                                    |                            |                                       |                 |                  |
| Equiti Foods Registration                                                                         |                                      | ×                          |                                       |                 |                  |
| Adolescent Survey                                                                                 |                                      | ×                          |                                       |                 |                  |
| - Socio-demographics (5 items)                                                                                |                                      |                            | ×                                     | ×               | ×                |
| - Symptoms (14 items)                                                                                         |                                      |                            | ×                                     | ×               | ×                |

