| - Chemotherapy-induced alterations in taste (13 items)                                                        |                                      |                            |                                       |                 | ×                |
| - Acceptability (2 items) and appropriateness (2 items)                                                       |                                      |                            |                                       |                 |                  |
| Parent Survey                                                                                     |                                      |                            |                                       |                 |                  |
| - Socio-demographics (15 items)                                                                               | ×                                    |                            |                                       |                 | ×                |
| - Food (6 items) and nutrition (6 items) insecurity                                                           | ×                                    |                            |                                       |                 | ×                |
| - Financial coping behaviors (18 items)                                                                       | ×                                    |                            |                                       |                 | ×                |
| - Personal Financial Wellbeing Scale (8 items)                                                                | ×                                    |                            |                                       |                 | ×                |
| - Participation in social roles and activities (12 items)                                                     | ×                                    |                            |                                       |                 | ×                |
| - Acceptable (4 items), appropriate (4 items), feasible (4 items), affordable (4 items), accessible (4 items) | ×                                    |                            |                                       |                 | ×                |

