#### 7.2.1 *Surveys and Interview Questions for Adolescents*

Adolescents will be asked to complete (a) a brief investigator-developed socio-demographic survey at baseline (T1), (b) established measures of alterations in taste and chemotherapy induced alterations in taste at weeks 4, 8, and 12 (T2-4) at the start of their semi-structured interviews, and (c) a person-reported measure of acceptability and appropriateness at week 12 (T4).

Socio-demographic items will ask the adolescent to tell us their current age (in years), sex at birth, race, the language they mainly use at home, and their current grade (year) in school.

---

Chemotherapy-induced alterations in taste will be measured by 13-items from the Chemotherapy-Induced Alterations in Taste Scale (CiTAS) [50]. Adolescents will be asked to use a 5-point scale to indicate how much the taste change bothered them this week. Scores will be calculated by summing item responses and dividing by 13 (lower scores indicate less alteration in taste).

Other chemotherapy-related symptoms will be measured by the 15-item Symptom Screening in Pediatrics (SSPedi) tool. [51] Adolescents will be asked to use a 5-point scale anchored by 0 (not at all) and 4 (worst bother) to indicate how much each symptom bothered them today or yesterday. Scores will be calculated by summing item responses. Scores can range from 0-60; lower scores indicate less symptom severity.

Semi-structured interviews will focus on the adolescent's experience with a study provided meal and their recommendations for improvements.

Adolescent-reported acceptability and appropriateness of the MTM-Kids program will be assessed using items that tap into each of these domain. The original items were developed and validated by Weiner and colleagues for use in studies that examine adopters' perspectives on the acceptability, etc. of implementing entire evidence-based programs in practice.[52] For this feasibility study, the Weiner, et al. items served as the basis for assessing areas that may affect participants' perspectives on specific aspects of the MTM program. Each domain has 4-items. Adolescents will be asked to read each item and indicate their response using 5-point scales anchored by 1=completely disagree and 5=completely agree. Domain scores will be calculated by summing item responses and dividing the sum by 4. Domain score range is 1-4, with higher scores indicating better acceptability or appropriateness.

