### **7.2.2 Surveys and Interview Questions for Parents**

Parents will be asked to complete established measures of household food and nutrition insecurity, time-demands, financial cost-coping behavior and financial wellbeing,

Household food insecurity will be measured by the 6-item Food Security Scale [53]. Parents will be asked to indicate whether they experienced the condition during the past 3 month and, in some cases, how often. Scores will be estimated by counting the number of affirmative responses (yes, sometimes, or often); these scores can be categorized, such that 0-1=very low food insecurity, 2-4= low food insecurity, and 5-6=high food insecurity. [53]

Household nutrition insecurity will be measured by the 4-item Nutrition Security Scale plus 2 items from the Healthfulness Choice Scale. [54] Parents will be asked to use a 5-point scale, anchored by 1=never and 5=always, plus a don't know/prefer not to answer option. Scores will be estimated by counting the number of affirmative responses (sometimes, often, or always); these scores can be categorized such that 0-

---

1=very low nutrition insecurity, 2-4= low nutrition insecurity, and 5-6=high nutrition insecurity. [54]

Parental role time-demands will be measured with a set of Patient-Reported Outcome Measurement System v.2 (PROMIS v.2) items that ask about satisfaction with perceived social role performance. [55] Parents will be asked to respond to the PROMIS items using a 5-point scale anchored by 1=not at all and 5=very much. Item responses will be summed and scored using the T-score metric. Higher scores indicate greater satisfaction with social role performance. [55]

Financial coping behaviors will be measured by 7 of the questions from the Financial Coping Behaviors Scale currently being asked in a study of financial distress during treatment of pediatric acute lymphoblastic leukemia (ALL; ACCL20N1CD). [56] Parents participating in MTM-Kids will only be asked about financial coping strategies with implications for the health of the adolescent or another family member. Parents will be asked to use a 3-point response scale anchored by 0=never and 2=several times) to indicate how often they used each coping behavior in the prior month. Item responses will be summed for a total score that can range from 0-14.[56]

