### 15.2.2.5 Financial Coping Strategies

Due to changes in your household expenses and work, have you done any of the following since your child was diagnosed (please select all that apply)?

|                                                                                  | Never | Sometimes | Often | I don't have this |
|----------------------------------------------------------------------------------|-------|-----------|-------|-------------------|
| Use savings                                                                      |       |           |       |                   |
| Use retirement funds                                                             |       |           |       |                   |
| Take out a loan or increase credit card debt                                     |       |           |       |                   |
| Get another job, or increase work hours                                          |       |           |       |                   |
| Not take a new job or opportunity because of worry about losing health insurance |       |           |       |                   |
| Receive money from fundraisers or crowdfunding                                   |       |           |       |                   |
| Cut back on putting in retirement or education accounts                          |       |           |       |                   |
| Move to reduce mortgage or rent                                                  |       |           |       |                   |
| Cut back on spending for vacation, travel, or relaxation                         |       |           |       |                   |
| Cut back on spending for afterschool or summer activities for your children      |       |           |       |                   |
| Cut back on spending for family celebrations                                     |       |           |       |                   |
| Cut back on spending for groceries                                               |       |           |       |                   |
| Cut back on spending for healthcare                                              |       |           |       |                   |
| Cut back on spending for necessities for your family, such as clothing           |       |           |       |                   |
| Cut back on spending for education                                               |       |           |       |                   |

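### Section 7.2, Table 1 and Appendix II contradict each other on the coping measure (7 items, prior month, 0-14, against 18 items since diagnosis) and the symptom measure (15 items, 0-60, against 14 items, maximum 56)

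*Protocol*

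**What the plan says.** **Coping.** Section 7.2.2 says "Financial coping behaviors will be measured by 7 of the questions from the Financial Coping Behaviors Scale", and that parents "will only be asked about financial coping strategies with implications for the health of the adolescent or another family member". The response scale has three points, from 0 for never to 2 for several times, with recall over the prior month. The scoring rule is "Item responses will be summed for a total score that can range from 0-14". Table 1 lists "Financial coping behaviors (18 items" in parentheses. The form in Appendix II (15.2.2.5) has 18 rows, among them use of savings, use of retirement funds, crowdfunding and cuts to vacation spending. Its columns are never, sometimes, often and "I don't have this". It asks about behavior since the child's diagnosis.

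**Symptoms.** Section 7.2.1 says "Other chemotherapy-related symptoms will be measured by the 15-item Symptom Screening in Pediatrics (SSPedi) tool", each item being scored 0 to 4. It adds "Scores can range from 0-60; lower scores indicate less symptom severity". Table 1 gives "Symptoms (14 items" in parentheses. The form in 15.2.1.4 has 14 symptom rows, from sadness to diarrhea.

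**Use.** Section 3.3.1 defines a signal as improvement at T4 compared with T1 and lists cost-coping among the outcomes. Section 8.3.3 reports means, ranges and SDs for both measures. Section 8 plans SDs and confidence intervals for signals of change, cost-coping included, and uses the upper limits of 80% intervals to plan the size of the future efficacy trial.

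**The concern.** A score is defined by its items, response codes, recall period and range. For coping, the text and the form disagree on all four. For symptoms, they disagree on the number of items and therefore on the range. Someone who fields the Appendix II forms and then scores them from section 7.2 cannot do what section 7.2 describes.

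For coping, two things are at stake: whether the T1-T4 comparison can show improvement at all, and whether the SD passed to the next trial belongs to a known scale. For symptoms, an item that was never asked at T2, T3 or T4 cannot be recovered by a later analysis plan, and the reported total would be set against a range that it cannot reach.

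**Working it through.** **1. The plan's own ranges, from section 7.2.** Maximum = number of items x maximum item score.
- Coping: 7 x 2 = 14. The stated 0-14 is reproduced.
- Symptoms: 15 x 4 = 60. The stated 0-60 is reproduced.

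The text is therefore consistent within itself. The conflict is between the text and the table and forms.

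**2. Rows on the Appendix II forms.** Coping has 18 rows and symptoms 14. Both counts match Table 1.

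**3. Ranges from the forms as printed.**
- Symptoms: 14 x 4 = 56. The shortfall is 60 - 56 = 4 points, or one item in 15 (1/15 = 7%), at each of T2, T3 and T4.
- Coping, all rows summed: 18 x 2 = 36. This assumes never/sometimes/often coded 0/1/2 and the fourth option coded 0 or missing. The form prints no codes.

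**4. Can 0-14 be formed from the coping form?** Arithmetically yes: any seven rows coded 0-2 sum to at most 14. But the protocol does not say which seven, and there are C(18,7) = 31,824 ways to choose seven rows from 18.

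**5. Coping, text against form.**

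| Feature | Section 7.2.2 | Appendix II form |
|---|---|---|
| Items | 7 | 18 (Table 1: 18) |
| Content | health-related strategies only | also savings, retirement, crowdfunding, vacation |
| Recall | prior month | since diagnosis |
| Top anchor | several times (2) | often (no code) |
| Fourth option | none | present, no score |
| Total | 0-14 | 0-36 if all rows are summed |

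The recall and anchor rows of this table apply to every item. Even with seven rows named, the form as printed would not give the prior-month frequency score that the text describes.

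**6. What the recall window does to T1-T4 change.** With prior-month recall, the T1 and T4 windows are separate, because the assessments are at least 12 weeks apart. With recall since diagnosis:
- T1 window = diagnosis to T1.
- T4 window = diagnosis to T4 = the T1 window plus the time from T1 to T4.

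The second contains the first. A parent who truthfully reports a behavior at T1 cannot truthfully answer never at T4, even if the behavior stopped on the day meals began. An item can improve only from often to sometimes, and only if the parent re-averages over a longer period.

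**The case against.** The strongest reply is that little depends on these scores. The primary benchmarks in 8.3.1 concern enrollment, survey completion, deliveries and interviews. Coping is exploratory. Symptoms are not a listed endpoint in section 3; they are summarized and linked qualitatively to interview themes. No cut-off or norm is applied, and the same 14 symptom rows are used at T2, T3 and T4, so comparison within the study is preserved. All of this stands, and it limits the weight of the point. It does not answer the coping recall conflict, which affects the T1-T4 comparison directly, or the use of cost-coping SDs in section 8.

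It can also be said that response coding belongs in a statistical analysis plan, which is not shown. That is fair for the code of the fourth option taken alone. It does not cover a form that asks different questions from those the text describes, because no analysis plan can change what was asked.

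A lost table row is not a plausible explanation for the symptom count, since Table 1 separately says 14.

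Some stronger readings are tempting, but the documents do not support them:
- *The coping form lacks the items that its score needs.* It has more rows than needed, and several have evident health relevance: groceries, healthcare, prescriptions, medication doses, appointments.
- *The coping total would be dominated by items outside the construct.* This assumes that all 18 rows are summed. The stated 0-14 range points to a seven-item score.
- *Eleven of the 18 rows are outside the construct.* That is only 18 - 7 = 11. The protocol does not classify the rows.

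**Conclusion.** The contradiction is real on both measures and should be resolved before the forms are used. It is an inconsistency between sections; the arithmetic in section 7.2 is sound.

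- **Symptoms:** the stated 0-60 range cannot be produced from the printed form, whose maximum is 56. This rests only on the row count and the 0-4 item scale.
- **Coping:** the seven scored items are unnamed, and the form differs from the text in recall period and anchors. It would run 0-36 instead of 0-14 if all rows were summed, under the assumed 0/1/2 coding. The recall period is the more serious defect: a since-diagnosis window at T4 carries baseline behavior forward and blunts the improvement that 3.3.1 looks for.

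An SD from a scale that might run to 14 or to 36 cannot be carried into the planning of the next trial until the scale is fixed. The consequences are confined to exploratory and descriptive results and to that planning step. The feasibility decision is not affected.

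**What to change.** Reconcile section 7.2, Table 1 and Appendix II before the forms are fielded.

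1. **Coping items.** Name the seven that form the 0-14 score. Either cut the form to those seven, or keep all 18 for description and score only the seven. The documents do not show which seven are meant, so the investigators must choose them.
2. **Coping recall and anchors.** Put the prior-month recall and the 0-2 anchors of 7.2.2 on the form.
3. **Fourth option.** State how "I don't have this" is handled. Zero and not applicable (missing) are both defensible: a household without retirement savings differs from one that chose not to draw on them. The rule should be fixed in advance.
4. **Symptoms.** Either add the fifteenth item, or declare a modified 14-item version scored 0-56 and correct 7.2.1. The documents do not list the 15 items, so the absent one cannot be identified from them.
5. **Table 1.** Make its item counts agree with the decisions above.

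The cost is form and text edits plus a protocol amendment, which section 11 requires the IRB to approve before implementation. Cutting the coping form to seven would spare each parent 18 - 7 = 11 items at each of the two surveys. Adding the symptom item would cost each adolescent one more item at each of T2, T3 and T4.

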## 8 STATISTICS

We will calculate descriptive statistics (frequency, proportion, central tendency, range, standard deviation [SD], reliability) to describe the study sample and estimate proportions, odds ratio, and confidence intervals (CI) for a priori feasibility benchmarks (see Time & Events Table). Feasibility study data can provide unreliable effect size estimates given small sample sizes. [46, 58] Thus, we will follow Brown [59] and estimate SDs and CIs for signals of change in food-related insecurities, cost-coping, time demands and QOL and use upper limits of 80% CIs plus enrollment and retention data to estimate sample size for the future efficacy trial. We will also consider evidence for associations between improvement in food security and QOL from studies of MTM with adult populations in estimating sample size for the future trial. [11, 44] Within days of an interview, two coders per interview will use rapid qualitative content analysis to analyze verbatim transcripts, compare their results and engage in discussion to resolve any discrepancies. The conceptual model (Figure 1) will guide the rapid analysis.[60] The goal is to identify actions at multiple levels (meal, child, household, study) to inform refinements for validation testing and ultimately the protocol for the future trial. When all interviews have been completed, we will use traditional content analysis to identify themes in the data overall to inform further refinements.

To ensure a rigorous and reproducible study, we have taken the following steps:

- Established a plan to enroll a diverse sample
- Justified the sample size
- Selected established measures to measure study variables
- Established the data analysis plan prior to data acquisition
- Considered relevant biological variables

Because sex hormones can affect taste function, processing of sweet and bitter, and food acceptability, [61] we will enroll similar numbers of biological female and male adolescents for each aim and explore the role of biological sex in the quantitative and qualitative data about alterations in taste and meal acceptability.

### 8.1 Study Design

This feasibility study uses a longitudinal design and multiple methods to determine the possibility of using the MTM-Kids study processes and intervention in a future full-scale RCT. 15 parent/adolescent dyads will be enrolled and asked to complete a survey at baseline (T1), receive MTM-Kids meals over 12 weeks, participate in interviews at 4, 8, and 12 weeks (T2, T3, T4) after starting to receive meals to inform refinement, and complete a follow-up survey at 12 weeks (T4).

### 8.2 Sample Size, Accrual and Duration of Accrual

#### 8.2.1 *Sample Size and Power*

The target sample size is 30 (15 adolescents + 15 parents). Sample size for this feasibility study is not based on an effect size, but rather is chosen based on logistic and financial considerations as well as the expertise of the researchers. The sample size is based on evidence that testing with five users identifies 85% of barriers and facilitators

---

to inform refinements, and three iterations of feedback per user during the testing period identifies 98% of barriers and facilitators to inform needed improvements in study processes and the intervention.

